### Statistical analysis

#### General analytical framework

The analysis of the association of the intervention with the outcome will generally be based on regression analysis, and will be performed according to the intention-to-treat principle [59]. While randomization will in general cause balance in the distribution of covariates, regression-based adjustment for covariates further strengthen the inference [60]. To accommodate the nested structure of the data and variable follow-up times in a regression framework, generalized linear mixed models (GLMM) with appropriate distributions and link functions will be used. We will use the GLIMMIX procedure in SAS (version 9.3, SAS Institute Inc., Cary, North Carolina, United States) to fit such models. All significance levels will be based on two-tailed *P* values at 0.05, except for *post hoc* exploratory and secondary analyses, which will be adjusted for multiple-comparisons.

#### Covariates

All the analyses will be adjusted for the following variables: age, sex, baseline level of asthma control, socioeconomic status (income and education), and coverage by any third-party insurance. We will also draw on administrative health records from the 12-month period before the study entry to measure other potential confounders such as comorbid conditions and general pattern of healthcare utilization (number of physician visits, hospitalization, and medication dispensations).

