#### Patients

Patients eligible for this study are individuals who fill a (incident or prevalent) prescription for ICS (either monotherapy or in a combination inhaler with long-acting beta-agonists) who answer affirmatively to the question ‘Have you ever been diagnosed by a doctor as having asthma?’. In line with the principles of pragmatic trials, our inclusion criteria are not overly restrictive so that the study sample remains representative of the target population. These inclusion criteria are similar to recent pragmatic trials in asthma [37] and are the following: 1) aged 14 years or older; 2) possessing a cellphone with the ability to send and receive text messages; 3) residing in BC, and planning to reside in BC for the next 12 months; 4) having been registered with the medical services plan (MSP, the provincial insurer of medically-required services) in the past 12 months, and planning to remain registered for the next 12 months; 5) not participating in another interventional study; 6) no communication difficulties, such as inability to communicate in English, or significant impairment in vision, hearing, or speech; and 7) consenting to participate in the study. Written informed consent will obtained from eligible patients before enrollment into the study.

We will utilize recruitment strategies used in our prior pharmacy practice studies [38–40], including posters and shelf-talkers. We will also advertise the study through various communication channels available to our research team, including the study website and social media. We will also implement strategies for targeting recruitment, including working closely with participating pharmacies to establish recruitment targets that are appropriate for the community they service. Furthermore, we will also implement regular monitoring of recruitment, including communication (for example, site visits, telephone calls, and/or emails) to discuss challenges and progress as well as offer ongoing support.

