### Data collection and study follow-up

The design of the trial and the schematic of data collection and outcomes are illustrated in Figure 2. Pharmacists will screen for eligibility, obtain informed consent, and enroll patients at their pharmacy. Upon patient enrollment, pharmacists will securely fax the individual’s contact information to the study research coordinator. Prospective data will be collected by telephone interview by an interviewer at set time points as follows: 1) sociodemographic characteristics, such as age, education, income, BC provincial health number (baseline); 2) Asthma Control Test and Asthma Quality of Life Questionnaire (AQLQ) (baseline, 6 months, and 12 months); and 3) changes in the enrollment of the individual with the provincial healthcare system, changes in third-party insurance, as well as the frequency of receiving inhaler medications through samples. In addition to prospectively collected outcome data, we will also obtain data for our study sample through BC PharmaNet (http://www.health.gov.bc.ca/pharmacare/pharmanet/netindex.html) [45] and Population Data BC (http://www.popdata.bc.ca) [46] In brief, these are extensive data resources for applied health services research with data holdings spanning information on all dispensed medications, includes drug name (brand and generic), Canadian Drug Identity Code, date dispensed, quantity dispensed, days of supply (BC PharmaNet), outpatient services, hospital separations, and vital statistics (Population Data BC).

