### Outcomes

The primary outcome is adherence to ICS ascertained by the medication possession ratio (MPR), the ratio of the days of medication supplied over the one-year follow-up [47], which will be calculated using BC PharmaNet data. Secondary outcomes include: 1) asthma control at the end of follow-up (measured by the Asthma Control Test [41]; 2) asthma-related quality of life (measured by using the AQLQ [48]); 3) asthma-related hospital admissions; and 4) use of reliever medications during the follow-up period (ascertained from the administrative health data).

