#### Analysis for objectives

To evaluate the impact of the EmPhAsIS intervention on our primary outcome of one-year adherence as measured by the MPR, we will use a random effects GLMM, assuming an approximate normal distribution and specifying an identity link function. The estimation will be based on GLMM with a random-effects term for pharmacy and fixed-effects terms representing the intervention as well as covariates. The same analytical framework as above will be used for secondary outcomes. The choice of the distribution and link function will depend on the scale and type of the dependent variable. For asthma control, a random-effects ordinal logistic regression model (GLMM with binomial distribution and cumulative logit link function) will be performed. Normal distribution and identity link function (equivalent of a linear mixed model) will be used to predict longitudinal changes in AQLQ and ACT.

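### The covariates fixed for the primary analysis leave out prior-year ICS adherence and new-user status, although the planned data linkage supplies both

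*Protocol article*

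**What the plan says.** The Covariates section of the protocol article gives a list for every analysis: "All the analyses will be adjusted for the following variables: age, sex, baseline level of asthma control". Income, education and third-party insurance coverage complete the list. The next sentence reads: "We will also draw on administrative health records from the 12-month period before the study entry to measure other potential confounders such as comorbid conditions". It then names a utilization measure, the "general pattern of healthcare utilization (number of physician visits, hospitalization, and medication dispensations"). No rule says whether or how these further variables enter a model. The Analysis for objectives section describes the primary model as a "GLMM with a random-effects term for pharmacy and fixed-effects terms representing the intervention as well as covariates", without saying which covariates.

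Four other places bear on the point:

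- **Patients:** eligibility covers "individuals who fill a (incident or prevalent) prescription for ICS", so new and established users are mixed. Registration with the provincial insurer over the past 12 months is required.
- **Outcomes:** the primary outcome is one-year ICS MPR, "which will be calculated using BC PharmaNet data".
- **Data collection and study follow-up:** the dispensing source holds "date dispensed, quantity dispensed, days of supply (BC PharmaNet") for all dispensed medications. Pharmacists screen, consent and enrol the patients.
- **Study design and Randomization:** under pharmacist-level randomization, the article names preferential recruitment of likely non-adherent patients by intervention pharmacists as a source of bias. It presents pharmacy-level randomization as removing such problems, but pharmacies cannot be blinded to their allocation.

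**The concern.** The list gives one secondary outcome, asthma control, its own baseline and does not do the same for the primary outcome. Two things are at stake.

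**Bias from recruitment.** Randomizing pharmacies does not balance patients who are recruited afterwards by staff who know the allocation. Pharmacists attend arm-specific webinars and then enrol their own patients, so the selection risk that the article describes for pharmacist-level randomization remains. It concerns prior adherence, the variable left out. Age, sex, income, education and insurance are indirect substitutes for it. If intervention pharmacists favoured poor adherers, as in the article's example, the effect would be understated; selection in the other direction would overstate it. An unequal mix of new and established users between arms is a second route, because new users have no prior ICS possession to compare.

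**Precision.** A baseline value correlated with the outcome reduces residual variance. The trial would already hold the data and not use them.

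**Working it through.** **Inputs from the article (Sample size calculation, General analytical framework):** difference 0.10 in MPR, two-sided alpha 0.05, power 80%, 1:1 allocation, ICC 0.06, five patients per pharmacy, N = 334 before attrition, 370 after.

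**Assumptions, not in the article:**
- r, the correlation between prior-year and follow-up MPR that remains beyond the listed covariates: 0.3 to 0.7 for bias, 0.3 to 0.6 for power.
- Equal SD for prior-year and follow-up MPR.
- ICC unchanged by adjustment.

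**Step 1: the plan's own figure.** The article states no SD for MPR, so it is solved from N.
- Design effect = 1 + (5 − 1) × 0.06 = 1.24.
- N = 2 × [2 × (1.960 + 0.842)² × SD² / 0.10²] × 1.24.
- Setting N = 334 gives SD = 0.293. With SD 0.293 and rounding up, 135 per arm × 2 × 1.24 = 334.8, or 335. SD 0.25 would give 246 and SD 0.30 would give 353.
- Attrition: 334 / 0.9 = 371, against 370 stated; 74 × 5 = 370. The figures are consistent with each other.

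**Step 2: bias if a recruitment difference in prior MPR is not adjusted for.** With equal SDs the regression slope is r, so bias ≈ r × difference.

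| Difference in prior MPR | r = 0.3 | r = 0.5 | r = 0.7 |
|---|---|---|---|
| 0.05 | 0.015 | 0.025 | 0.035 |
| 0.10 | 0.03 | 0.05 | 0.07 |

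Against the target of 0.10, the first row is 15% to 35% of the effect sought, and the second is 30% to 70%.

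**Step 3: power if prior MPR is adjusted for.** Residual SD = 0.293 × √(1 − r²). The unadjusted standard error is 0.10 / 2.802 = 0.0357, so power = Φ(2.802 / √(1 − r²) − 1.96).

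| r | Residual SD | Power at 334 | N for 80% power |
|---|---|---|---|
| 0 | 0.293 | 80% | 335 |
| 0.3 | 0.279 | 83.6% | 306 |
| 0.4 | 0.268 | 86.4% | 283 |
| 0.5 | 0.254 | 89.9% | 253 |
| 0.6 | 0.234 | 93.8% | 216 |

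At r = 0.2 the same formula gives Φ(2.859 − 1.96), about 82%, so a weak correlation buys little.

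**Step 4: is the gap closed elsewhere?** The sentence on pre-entry records promises to measure confounders and gives examples. Its closest example is a utilization measure based on medication dispensations. It is not stated to be ICS-specific, is not a possession ratio, and is not assigned to the primary model. Incident or prevalent status appears only as part of eligibility.

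**The case against.** The strongest reply is that this is a condensed article, and the full protocol or analysis plan may define the final covariates. The list of prior-year confounders is illustrative, and prior ICS dispensing would fit within it. That stands in part: the article touches prior dispensing and does not exclude an ICS-specific measure. But it chooses to fix a list for all analyses, and that list omits the baseline of the primary outcome while leaving the rest open.

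Other parts of the reply also stand. Chance imbalance is already reflected in the standard error and does not bias a randomized comparison; the bias argument rests on recruitment after allocation. Baseline asthma control and the prior-year variables, if they enter, would absorb some of the imbalance. The correlation and the SD are assumptions. The 80% starting point gives the listed covariates no credit, and the ICC could change after adjustment.

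Three stronger readings are tempting but not supported:

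- **That these are the strongest predictors of follow-up MPR.** Nothing in the article ranks predictors or shows that new and established users differ in follow-up MPR. It is plausible, no more.
- **That the trial is undersized.** The calculation takes no credit for covariates, so the omission makes neither 334 nor 370 wrong.
- **That AQLQ likewise lacks its baseline.** AQLQ is collected at baseline, 6 and 12 months, and the Analysis for objectives section models longitudinal change in it, which may already use the baseline value.

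**Conclusion.** The point holds as a weakly fixed adjustment set, not as an arithmetic error or a contradiction. The committed covariates omit prior-12-month ICS MPR and new-user status, the planned data can supply both, and no other sentence commits an equivalent to the primary model.

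The main consequence is exposure to recruitment imbalance that the design leaves open: about 0.015 to 0.035 on the MPR scale for a 0.05 difference in prior MPR, if r lies between 0.3 and 0.7. The article does not show that such a difference will occur. The second consequence is forgone precision: power of about 84% to 94% instead of 80% for r of 0.3 to 0.6. Both ranges depend on the assumed r, taken as beyond the listed covariates; the power range also depends on the back-solved SD of about 0.293.

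**What to change.** Before outcome data are seen:

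1. Name two covariates of the primary model in addition to the present list: ICS MPR over the 12 months before entry (set to 0 for new users) and a new-user indicator. The indicator separates patients with no earlier ICS supply from established users who possessed very little.
2. State whether the other potential confounders enter the primary model and, if so, which ones and by what rule.

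The cost is a few lines of text and a small amount of variable derivation from records already planned, with no new data collection. One definition needs care: patients who started ICS during the look-back year are neither new nor full-year users, so the plan must say which denominator their prior MPR uses and how the indicator classes them. The sample size can stay as it is, with the gain in precision held as a margin.

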#### Analysis for objectives

To evaluate the impact of the EmPhAsIS intervention on our primary outcome of one-year adherence as measured by the MPR, we will use a random effects GLMM, assuming an approximate normal distribution and specifying an identity link function. The estimation will be based on GLMM with a random-effects term for pharmacy and fixed-effects terms representing the intervention as well as covariates. The same analytical framework as above will be used for secondary outcomes. The choice of the distribution and link function will depend on the scale and type of the dependent variable. For asthma control, a random-effects ordinal logistic regression model (GLMM with binomial distribution and cumulative logit link function) will be performed. Normal distribution and identity link function (equivalent of a linear mixed model) will be used to predict longitudinal changes in AQLQ and ACT.

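### The longitudinal ACT and AQLQ analyses inherit the one-value-per-patient MPR model, with no visit term, patient-level term or baseline AQLQ named

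*Protocol article*

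**What the plan says.** All of this is in the protocol article.

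- **Analysis for objectives, primary outcome.** One-year MPR is modelled with a normal distribution and identity link: "The estimation will be based on GLMM with a random-effects term for pharmacy and fixed-effects terms representing the intervention as well as covariates". MPR gives one value per patient.
- **Same section, secondary outcomes.** "The same analytical framework as above will be used for secondary outcomes". The text adds only that distribution and link will depend on the type of outcome. Asthma control gets an ordinal logistic model with random effects. For the scores, "Normal distribution and identity link function (equivalent of a linear mixed model) will be used to predict longitudinal changes in AQLQ and ACT".
- **Data collection and study follow-up.** The interviews collect "Asthma Control Test and Asthma Quality of Life Questionnaire (AQLQ) (baseline, 6 months, and 12 months".
- **Covariates.** All analyses adjust for "age, sex, baseline level of asthma control, socioeconomic status (income and education), and coverage by any third-party insurance". Administrative-data measures of comorbidity and healthcare use may be added. Neither baseline AQLQ nor visit is listed.
- **General analytical framework.** Mixed models are chosen "To accommodate the nested structure of the data and variable follow-up times in a regression framework". The levels of nesting are not listed.

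**The concern.** A pharmacy random intercept is enough for MPR, because patients within a pharmacy are the only correlated units. ACT and AQLQ add a level: three visits within each patient. The section assigns the MPR model to these data and names neither a patient-level covariance nor a visit or intervention-by-visit term. A difference between arms in change is an intervention-by-visit contrast, so the quantity to be estimated is left open. It could be a time average, a 12-month contrast or a change score.

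Two things are at stake for these secondary analyses: a treatment effect diluted by baseline rows, and a change contrast tested with an inflated standard error. In addition, the most useful covariate for AQLQ, its own baseline, is collected but not in the list.

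**Working it through.** **Inputs.** The document gives no power or precision figure for ACT or AQLQ, so there is none to reproduce. From Sample size calculation: 74 pharmacies of 5, so 370 patients, with 37 pharmacies per arm and ICC 0.06 (chosen there for adherence and borrowed here). Three visits. Nominal two-sided 5%. Assumed, not in the document: outcome SD 1, within-patient correlation r from 0.3 to 0.8, no pharmacy-by-visit variance and, for the closed forms, complete data. The variance splits into pharmacy 0.06, patient r − 0.06 and residual 1 − r.

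**1. Literal model, baseline rows included.** With effect 0 at baseline and δ at 6 and 12 months, the intervention coefficient estimates (0 + δ + δ)/3 = 2δ/3. An effect of 0.30 SD becomes 0.20. Simulated fits gave 0.196 and about 0.21. With 6- and 12-month rows only, there is no such dilution.

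**2. Intervention-by-visit added, pharmacy the only random term, no baseline covariate.**

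- True SE of the 0-to-12-month contrast: √[8(1 − r)/370].
- Model SE: √[8·MSE/370], with MSE = [296{(1 − r) + 3(r − 0.06)} + 736(1 − r)]/1032. Here 296 = 74×4, 736 = 370×2 − 4 and 1032 = 296 + 736.
- With q the ratio of the two, type I error = 2Φ(−1.96q). Power, where the correct model has 80%, = Φ(2.80 − 1.96q).

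At r = 0.5: MSE = (296×1.82 + 736×0.5)/1032 = 0.879, model SE 0.138, true SE 0.104, q = 1.33.

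| r | true SE | model SE | ratio | type I error | power |
|---|---|---|---|---|---|
| 0.3 | 0.123 | 0.140 | 1.14 | 2.6% | 72% |
| 0.5 | 0.104 | 0.138 | 1.33 | 0.9% | 58% |
| 0.7 | 0.081 | 0.136 | 1.68 | 0.1% | 31% |
| 0.8 | 0.066 | 0.135 | 2.05 | 0.01% | 11% |

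Simulation (1000 runs per setting) gave ratios of 1.13, 1.32 and 1.67 at r = 0.3, 0.5 and 0.7. With unequal pharmacy sizes and about 10% loss at each follow-up visit, they were 1.29 at r = 0.5 and 1.55 at r = 0.7.

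**3. Where the pharmacy-only SE is right.** In the same simulations the intervention main effect had SE ratios of 1.00 to 1.02 and rejection rates of 4.4% to 6.0%. One 12-month change score per patient had ratios of 1.02 to 1.04 and rejection rates of 4.1% to 5.1%. For the main effect, the pharmacy component absorbs the patient variance.

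**4. Effect of the listed baseline covariate.** Within a pharmacy, the three-visit patient mean has variance a = (r − 0.06) + (1 − r)/3.

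- *ACT, own baseline as covariate on all rows.* This removes a²/0.94. At r = 0.8: a = 0.8067, leaving 0.1144. MSE = (296×3×0.1144 + 736×0.2)/1032 = 0.241, ratio √(0.241/0.2) = 1.10. At r = 0.3 the ratio is 1.00.
- *AQLQ, baseline ACT as covariate, with an assumed cross-scale correlation c.* This removes c²/0.94. At r = 0.7 and c = 0.4: a = 0.74, leaving 0.570. MSE = (296×3×0.570 + 736×0.3)/1032 = 0.704, ratio √(0.704/0.3) = 1.53. With c = 0.6, 0.357 is left, MSE = 0.521 and the ratio is 1.32.

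The inflation is therefore mainly an AQLQ matter.

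**5. Gain from own-baseline adjustment, r = 0.6.** A small simulation (25 runs, so rough) gave a 12-month SE of 0.087 with own baseline, 0.095 for a change score and 0.108 with baseline ACT only. Approximate closed forms agree:

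- Change score: √(8×0.4/370) = 0.093.
- Own baseline, ignoring pharmacy: 0.093×√[(1 + 0.6)/2] = 0.083.
- Baseline ACT only, with c = 0.4: √(4×1.24/370)×√(1 − 0.16) = 0.106.

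**The case against.** The best defence is that the article does not say pharmacy is the only random effect. The sentence naming it describes the MPR model. General analytical framework refers to nesting and follow-up times, which leaves room for patient and visit. Covariance structure and visit coding are ordinarily left to an analysis plan. The phrase "will be used to predict longitudinal changes in AQLQ and ACT" may also mean one change score per patient, for which a pharmacy intercept suffices. Finally, the named asthma-control outcome is control at the end of follow-up, one value per patient with its own ordinal model, so longitudinal ACT is a further analysis.

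Most of this stands. A reader might infer that the standard errors are simply wrong, or that a real benefit would probably be missed. The document does not support either claim. The inflated SE needs a particular combination: repeated rows, an intervention-by-visit term and no patient term. Even then the loss is modest at low correlation or for baseline-adjusted ACT. Nor does the text say that baseline ACT is both a response and a covariate.

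What the defence does not remove is that the section goes into model terms, assigns a single-measurement model to three-visit scores, and says only that distribution and link will vary. It also fixes a covariate list without baseline AQLQ.

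**Conclusion.** The point holds as a minor one. The model written for MPR is carried to three-visit ACT and AQLQ data, and the estimated quantity is left undetermined. Depending on the reading, a constant effect is diluted to two thirds (baseline rows kept, no intervention-by-visit term), the change contrast has an SE 1.1 to 2.0 times too large (intervention-by-visit added, no patient term, no baseline adjustment), or nothing is wrong (main effect on follow-up rows only, or one change score per patient). Where the SE is wrong it is too large, so the cost is power and not false positives. This holds as long as baseline ACT does not correlate more strongly with AQLQ than AQLQ does with itself across visits.

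All correlations are assumptions, and the ICC is borrowed from adherence. Only secondary outcomes are affected. The MPR analysis is not.

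**What to change.** For AQLQ and longitudinal ACT, state that:

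- the responses are the 6- and 12-month scores;
- the fixed effects are intervention, visit, intervention-by-visit, the outcome's own baseline value and the listed covariates, with baseline AQLQ added to the list;
- the random part is a pharmacy intercept plus either a within-patient covariance or a patient intercept nested in pharmacy;
- the estimate is the 12-month contrast between arms.

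If one change score per patient is intended, say so. Its SE is valid, though own-baseline adjustment is more precise.

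The cost is one sentence and one extra RANDOM statement in GLIMMIX. Baseline AQLQ is already collected, so no new data are needed.
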